### Primary outcome

The primary outcome will compare the rate of CVC-free days following index AV access surgical creation. The total duration of CVC-free days will be determined for each patient and calculated for the whole cohort per 100 patient-days of study follow-up. In patients who undergo placement of a second AV access after abandonment of the index access, the total CVC-free days may include two or more discrete time segments of CVC independence interposed between periods of CVC dependence.

### Safety outcome

Safety between AVF and AVG strategy will be compared as aggregate rates of vascular access-related (CVC or AV access) infections that lead to hospitalization or death.

### Secondary, tertiary and other outcomes

The secondary outcome will compare vascular access-related healthcare costs; rates of AV access maturation; rates of AV access adjuvant procedures; rates of infectious and non-infectious vascular access (CVC or AV access) complications; and deaths. Event definitions for AV access outcomes and CVC outcomes, and cause of death categorization are listed in **Additional file 4**. Standard costs attributed to vascular access (index AV access, CVC, new AV access) adjuvant interventions and complications will be used to calculate cumulative access-related costs between the two groups (**Additional file 5**).

Tertiary outcomes consist of patient-reported outcomes. Patients’ satisfaction with their dialysis vascular access will be elicited with the Vascular Access Questionnaire [21] and the Decision Regret Scale [22]. Health-related quality of life will be assessed with the EuroQol 5-dimension 3-level [23]. Patient’s preferences between quality/quantity of life and future/present health will be assessed with the Attitude Scale [24] and SUPPORT questionnaire [25]. These instruments are described in **Additional file 6**.

Exploratory outcomes will evaluate for relationships between preoperative frailty measures and the rate of index AV access primary failure, time to successful AV access cannulation, and the rate of adjuvant procedures on index AV access.

## Participant timeline

Recruitment is projected over 2.5 years. We target an average follow-up period of 2 years from the date of randomization.

## Data collection

The schedule of assessments is summarized in Table 3. Participant’s baseline physical function will be assessed with objective tests (i.e., Grip Strength [26] and Chair stand [27]) and subjective instruments (i.e., Pepper Assessment Tool for Disability [28] and Clinical Frailty Scale [29]). Data will be collected prospectively through monthly review of electronic medical records for events documented at outpatient dialysis units, outpatient clinics, outpatient or inpatient interventional nephrology/interventional nephrology, and inpatient charts. We will record receipt of allocated index AV access (date of surgery, type of AV access surgery performed [AVF or AVG] and anatomical description, and attending surgeon’s expertise [number of new AV access surgeries performed in the 12 months prior to study start-up]). Medical events of interest, listed in **Additional file 7**, will be recorded with the diagnoses deemed by the treating medical team. Questionnaires will be administered pre-randomization and during follow-up at months 6, 12, 18 and 24 via telephone interviews. Time points for questionnaires administration are calculated from the date of randomization. The type(s) of vascular access a patient has at the time of questionnaire administration will be documented as either CVC, index AV access, and/or new AV access. At each clinical center, study coordinators responsible for questionnaire administration and data collection have received in-depth training in all study-related operational procedures, data collection, and data entry. Events of major or non-major protocol deviation and drop-out will be monitored and recorded (**Additional file 8**).

**Table 3 Tab3:** Schedule of Evaluations

Assessment	Pre- & Screening	Baseline at randomization	Study Surgery	Schedule in Months			
				M6	M12	M18	M24
Medical history*	X	X					
Duplex ultrasound of vessels, pre-op^£^	X						
Consent Capacity Assessment		X					
Informed consent		X					
Demographics*	X						
Living situation		X					
Highest scholastic education achieved		X					
Medical Insurance*		X					
Nephrology care background*		X					
Medications*		X					
Blood laboratory data*		X (monthly)					
End-stage kidney disease history*	X						
Past AV access history*		X					
CVC history*		X					
Randomization group		X					
Surgeon expertise			X				
Index AV access description			X				
Antibiotic administered peri-op			X				
Grip Strength^†^		X					
Chair Stand test^†^		X					
Pepper Assessment Tool for Disability		X ^#^					
Clinical Frailty Scale^§^		X ^#^					
EuroQol 5-dimension 3-level^€^		X ^#^		X	X	X	X
Vascular Access Questionnaire score^€^		X ^#^		X	X	X	X
Attitude Scale (Tradeoffs)^€^		X ^#^		X	X	X	X
SUPPORT questionnaire^€^		X ^#^		X	X	X	X
Decision Regret Scale^€^				X	X	X	X
Duplex ultrasound of AV access				X (monthly)			
Hospitalizations (length and cause)		X (monthly)					
CVC complications^¶^		X (monthly)					
CVC removal / reinsertion		X (monthly)					
Adjuvant endovascular interventions^‡^				X (monthly)			
Adjuvant surgical interventions^‡^				X (monthly)			
AV access complications^¶^				X (monthly)			
Successful cannulation				X (monthly)			
AV access maturation failure				X (monthly)			
New AV access creation				X (monthly)			
Type of vascular access used for HD		X (monthly)					
End-of-study event^¥^		X (monthly)					
Serious Adverse Events		X (monthly)					

*Electronic medical records review

^£^Data collection when preoperative duplex ultrasound vascular mapping was performed

^†^Obtained in-person

^‡^Pertaining to AV access (index or new AV access) or CVC. ^§^Instrument will be completed by the treating physician. ^¶^Infectious and non-infectious complications and treatment

^¥^End-of-study event represents a drop out event (withdrawal of consent, withdrawal from the study, transition to peritoneal dialysis, transition to home HD, transfer of care outside participating health system network, kidney transplantation and successful discontinuation of HD, death) or end-of-study date

^€^Questionnaire administration between study coordinator and participant may take place in-person or via telephone

^#^Baseline questionnaires will be completed before index AV access surgery date or within 10 working days from the date of informed consent, whichever comes first

AV denotes arteriovenous; CVC, central venous catheter; HD, hemodialysis; M, month. Assessment time points for follow-up questionnaires will be set from the date of randomization

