## Outcomes and measurements

All the outcomes, summarized in Table 1, are measured from the date of randomization to end-of-study event (i.e., drop out event or end-of-study date).

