### Analysis for primary outcome

The primary outcome is the rate of CVC-free days per 100 patient-days. The primary analysis will be performed under the intention-to-treat principle. The outcomes will be measured from the date of randomization to the date of an end-of-study event (see **Additional file 7**) or end-of-study date, whichever comes first. For each participant, the primary outcome will be the cumulative number of days that dialysis is delivered using AV access with the at-risk time as an offset. We will compare outcomes between the treatment groups using Poisson regression, modeling the number of CVC-free days as the dependent variable with a log link, the treatment assignment as the predictor, and the natural log of number of at-risk days as an offset. Covariate adjustment will include enrollment center and history of prior AV access. Analyses will take into account events of CVC re-use after CVC-free days. Deviance residuals and the overall deviance measure will be calculated to assess the overall goodness of fit of the model as part of model diagnostics. If we observe overdispersion, we will explore the negative binomial models. Sensitivity analyses will be performed in the as-treated and per-protocol populations.

As a supporting analysis, safety analysis will be conducted to examine severe access infections defined as infections requiring hospitalization or death caused by access infection. Rates of severe infections between AVG and AVF groups will be compared using Poisson regression models. If we observe overdispersion, we will explore the negative binomial models.

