One important limitation of this RCT is that we have restricted eligibility to patients who have already started HD. After careful consideration, we elected not to include pre-ESKD patients undergoing AV access surgery for several reasons. First, as these patients are not CVC-dependent, the primary study endpoint (duration of CVC-independence) would be less meaningful. Second, in the absence of a CVC, catheter-related infections (the primary safety outcome) would not occur. Third, it is not possible to definitively ascertain whether an AVF is mature until the patient starts HD and cannulation is attempted. In clinical practice, although it is preferred that patients undergo AV access surgery within 6–9 months prior to the anticipated start date of dialysis, time to HD initiation is often difficult to ascertain [63]. Fourth, pre-ESKD patients with an AV access tend to undergo fewer AV access adjuvant procedures than their counterparts on HD due to the fact that they are seen less often by their nephrology providers and there is less impetus to re-intervene on and accelerate development of an existing AV access when HD had not been initiated [53].

A second limitation of this study is the potential bias regarding physicians’ decision on whether a certain type of AV access might be preferentially considered on an individual basis. Although the recent observational studies support equipoise in clinical outcomes between AVF and AVG in older CVC-dependent HD patients with comorbid conditions, not all providers recognize such equipoise. To prevent the occurrence of ascertainment bias, emphasis was placed during training on the expectation that nephrology and surgery providers should exercise unbiased determination of surgical suitability for AVF and AVG among study candidates. When a potential candidate is deemed ineligible for either AVF or AVG, the reason for particular AV access ineligibility is documented and discussed during monthly web-based meetings with all site investigators.

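### Leaving the study, as distinct from withdrawing consent, truncates outcomes that are read from charts; this avoidable loss can bias the intention-to-treat comparison

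*Protocol article*

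**What the plan says.** The Table 3 footnote (Data collection) defines the end-of-study event as "a drop out event (withdrawal of consent, withdrawal from the study", followed by further events such as transfer of care, transplantation and death. Withdrawal of consent and withdrawal from the study are thus two separate items.

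Both close the outcome window. Under Outcomes and measurements, all outcomes "are measured from the date of randomization to end-of-study event (i.e., drop out event or end-of-study date"; under Analysis for primary outcome, "The outcomes will be measured from the date of randomization to the date of an end-of-study event" or the end-of-study date, whichever is earlier. The same section states: "The primary analysis will be performed under the intention-to-treat principle". The model is a Poisson regression with "the natural log of number of at-risk days as an offset".

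Table 1 gives chart review as the source for the primary, safety, cost, infection, hospitalization and survival outcomes. Data collection adds: "Data will be collected prospectively through monthly review of electronic medical records". Inclusion criterion 7 requires that the research team can reach these records. After baseline, only the questionnaires at months 6, 12, 18 and 24 need the participant.

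**The concern.** A participant may stop contact with the study and yet not withdraw consent. The charts of such a person remain readable, and monthly review is already running, but the rule ends measurement on the day the person leaves. That is wider than the data source requires, and it sits uneasily with the aim, under Data monitoring and quality assessment, of making every effort to obtain all data points.

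Treating providers and investigators cannot be blinded, and the assignment is passed to the surgical team before the operation. Leaving after the assignment is known may therefore depend on arm and on prognosis. If it does, the rates compared are no longer those of everyone randomized over the intended follow-up, and the protection that intention-to-treat analysis should give is weakened where the missing data could have been collected.

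**Working it through.** **1. Reading the rule.**
- Event: study withdrawal, listed beside consent withdrawal (Table 3 footnote).
- Consequence: all outcomes end there (Outcomes and measurements; Analysis for primary outcome).
- Source of the affected outcomes: charts (Table 1; Data collection).
- What does not end follow-up: postponed, missed or cancelled index surgery is recorded with its reason (Adherence to allocated intervention) and is not in the event list; participants who receive a new access stay in follow-up (New AV Access surgery).
- What is kept: days before withdrawal, because the offset is at-risk days. Follow-up is truncated and the participant is not deleted.

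Everyone enters on a catheter. Someone who leaves at day 30 of an average 730 contributes 30/730 = 4.1% of the planned time, probably all of it catheter-dependent.

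**2. The plan's own power figure.** Inputs from the sample size section: 131 per group, 25% drop-out (131 × 0.75 ≈ 98), 730 days, 15 against 20 per 100 patient-days, two-sided 5%. The variance of the log rate ratio is 1/(98 × 730 × 0.15) + 1/(98 × 730 × 0.20) = 0.000163, so its standard error is 0.0128. With ln(20/15) = 0.288, power under a pure Poisson model exceeds 99.9%. The stated lower bound of 90% is met. This figure does not bear on bias, and the 25% is not split by cause, so the share due to study withdrawal is unknown.

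**3. Illustration of possible bias.** All inputs here except the 730 days and the rates are assumptions. Let stayers have rate r (0.15 AVF, 0.20 AVG) over T = 730 days. A share w leaves at day t = 30 with no catheter-free days so far and would then run at m times the stayers' rate.

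- Truncated rate = (1 − w)·r·T / [(1 − w)·T + w·t]
- Rate with chart review continued = r·[(1 − w) + w·m·(T − t)/T]

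With equal w in both arms, the truncated ratio is always 0.20/0.15 = 1.333. For w = 0.10, the bracket is 0.9 + 0.1 × 700/730 = 0.9959 when m = 1, and 0.9 when m = 0. Hence:
- AVF leavers at m = 0, AVG leavers at m = 1: 1.333 × 0.9959/0.9 = 1.475
- AVG leavers at m = 0, AVF leavers at m = 1: 1.333 × 0.9/0.9959 = 1.205

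| Share leaving, each arm | Truncated ratio | Ratio with chart review continued |
|---|---|---|
| 5% | 1.333 | 1.269 to 1.401 |
| 10% | 1.333 | 1.205 to 1.475 |
| 25% (whole drop-out allowance) | 1.333 | 1.010 to 1.760 |

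Setting m = 2 for AVF leavers instead gives 1.272, 1.216 and 1.073, inside these ranges.

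**4. When there is almost no bias.** If leavers later match the stayers of their own arm (m = 1 in both), unequal leaving alone does little. With 25% of AVF and 10% of AVG leaving at day 30, the ratio moves from 1.342 to 1.345 (+0.3%); at day 90, from 1.359 to 1.369 (+0.8%). Material bias needs leaving to be related to later catheter-free days, and differently in the two arms.

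**The case against.** Four points can be made against this.

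- **The term is not defined here.** The article refers drop-out and end-of-study detail to Additional files 7 and 8, which are not shown and may define it narrowly. That stands as a caution. But the published rule lists the event separately and ends every outcome at it, so it is a stated rule and not just a missing detail.
- **Consent is the legal basis.** Data management rests data use on consent to participate, so some who leave will thereby end permission for chart review. That also stands: the criticism covers only those whose permission remains, and the document does not show how many they would be.
- **Informative censoring is provided for.** The Missing data section plans multiple imputation and shared-parameter or pattern-mixture models. These mitigate the problem, but they rest on assumptions about unseen data and leave the primary estimate truncated.
- **Differential withdrawal is not shown.** The Discussion's remark that "not all providers recognize such equipoise" concerns judging candidates' suitability before randomization. It does not show that people leave after allocation.

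A reader might also infer that declining the allocated surgery or stopping the questionnaires removes a participant. The document does not say so. Missed surgery is recorded without ending follow-up, as-treated and per-protocol sensitivity analyses are planned, and surgical adherence, chart review and questionnaires are monitored as separate components.

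**Conclusion.** The point holds as a possible, avoidable source of bias, and correcting it is a cheap improvement. The rule is in the current text, reaches the primary outcome, and discards data that could be read from charts wherever permission to use records remains. In an open trial this can bias the intention-to-treat comparison.

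A reader might go further and conclude that the comparison is biased, or put a size on it. One could assume that 5% to 10% of one arm leave and differ from stayers by 15 to 20 per 100, giving shifts of 0.05 × 15 = 0.75 to 0.10 × 20 = 2.0 points, or 15% to 40% of the 5-point target. The document supports neither step. Every input except the target is assumed. A shortfall above 15 is impossible against an AVF rate of 15 per 100, and a shortfall of 20 against an AVG rate of 20 requires no catheter-free days at all. No withdrawal rate by arm is given, so size and direction remain unknown. The ratios in the table show only what could happen under the stated assumptions, from under 1% when leavers resemble stayers to a material change when they do not.

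**What to change.** - Distinguish two acts: stopping study contact or questionnaires, and withdrawing permission to use medical records.
- For chart-based outcomes, remove study withdrawal from the events that end at-risk time. Continue monthly chart review until permission for record use is withdrawn or another listed end-of-study event occurs.
- Tabulate both kinds of withdrawal by arm.

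The cost is an amendment to protocol and consent wording. No visits are added, since monthly chart review already runs. The article reports the trial as still enrolling, with completion estimated for the end of 2026, so at that stage the change could still cover much of the follow-up. It brings no gain for participants who also withdraw permission for record review. For those already enrolled, its reach depends on what they agreed to in the consent form.

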## Randomization

After informed consent is obtained, a member of the study team at each clinical center enacts the randomization through the centralized REDCap platform (Fig. 1). The randomization system is based on a block-permutation scheme with variable (two to four) block sizes, and assigns participants in a 1:1 ratio to AVG or AVF placement, stratified by (a) clinical center and (b) history of previous AV access surgery.

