## Blinding

Due to the visible nature of the intervention, blinding of the treating providers and investigators is not possible. Although the study intervention is unmasked, the clinical outcomes collected in the study are informed by medical diagnoses judged by the treating providers, independent of the study.

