### Adherence to allocated intervention of index AV access surgery

After informed consent is obtained, the randomization assignment (i.e., type of index AV access to be surgically created) will be relayed to the vascular surgery team through verbal and electronic mail communication. Surgical intervention adherence to the assigned, index AV access is monitored during the study. All events of index AV access surgery postponement, missed surgery, or cancellation, with or without rescheduling, will be recorded along with the reason for such events.

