### Analysis for tertiary outcomes

Vascular Access Questionnaire scores will be obtained at 6, 12, 18 and 24 months during follow-up. We will use a linear mixed-effects model approach to compare the postoperative Vascular Access Questionnaire scores between AVF and AVG groups and to examine the longitudinal pattern in the Vascular Access Questionnaire scores over time within each treatment group. The model will include an indicator variable for treatment (AVF vs. AVG), time, and treatment by time interaction. Least square means for each group will be reported. We will test for treatment effect overall and at each time point using contrasts. Covariate adjustments will include baseline scores and the ones similar to the models used in the analysis for the primary outcome. For analyses of EQ-5D, Regret, and Tradeoffs, we will use a similar approach. For analysis of *goal concordant care regarding vascular access approach*, each participant will be classified as being concordance or not at each follow-up visit. A generalized estimating equation (GEE) model will be fit to compare the likelihood of being concordance between the AVG and AVF groups. Odds ratios (OR) averaged over time and at each time point will be reported.

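### Table 3 lets baseline questionnaires be completed after open-label allocation, against the text's pre-randomization rule; three baseline-adjusted tertiary analyses could be biased

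*Protocol article*

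**What the plan says.** Two places in the protocol article time the same baseline instruments.

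- Data collection, main text: "Questionnaires will be administered pre-randomization and during follow-up at months 6, 12, 18 and 24 via telephone interviews".
- Table 3, footnote #: "Baseline questionnaires will be completed before index AV access surgery date or within 10 working days from the date of informed consent", whichever is earlier. The mark is attached to the Pepper disability tool, Clinical Frailty Scale, EQ-5D, Vascular Access Questionnaire, Attitude Scale and SUPPORT. The footnote does not mention randomization.

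The surrounding sequence is as follows.

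- Randomization: "After informed consent is obtained, a member of the study team at each clinical center enacts the randomization through the centralized REDCap platform". No interval from consent is given, and no completed questionnaire is required first.
- Adherence to allocated intervention: after consent, "the randomization assignment (i.e., type of index AV access to be surgically created) will be relayed to the vascular surgery team".
- Blinding: "blinding of the treating providers and investigators is not possible".
- Study coordinators at the centers administer the questionnaires, and the treating physician completes the Clinical Frailty Scale (Data collection and Table 3 footnotes).

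The scores are used in two ways. For the Vascular Access Questionnaire mixed model, "Covariate adjustments will include baseline scores", and a similar approach is planned for EQ-5D, Regret and Tradeoffs (the Attitude Scale). The frailty and disability scores go into a composite predictor in the exploratory models of access primary failure.

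**The concern.** A baseline covariate is safe to adjust for because allocation cannot have influenced it. If the score is taken after an open allocation, that protection is lost. A patient who knows which access is planned may rate access satisfaction or trade-offs differently, and an interviewer or rater who knows the arm may influence the record. Adjusting for such a score can remove part of a real treatment effect or create one where none exists.

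The outcomes concerned are subjective, and the Discussion names patient satisfaction as one of the three questions the trial sets out to answer. A center that follows the footnote can break the rule in the main text without noticing, and no later analysis can recover a pre-allocation baseline that was not collected.

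**Working it through.** **Step 1: can the two timing rules be one rule?** The type of index surgery is the randomized allocation, so surgery always comes after randomization. If every baseline had to precede randomization, a limit set at surgery could never bind. That part of the footnote has an effect only if completion between randomization and surgery is allowed. The consent-based limit does not help either: randomization also follows consent, at an unstated interval, and may fall inside the 10 working days. The footnote therefore permits completion after allocation, while the main text does not.

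**Step 2: which analyses does this reach?**

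| Instrument | Baseline taken | Use of the baseline | Reached by the adjustment bias? |
|---|---|---|---|
| Vascular Access Questionnaire | Yes | Covariate in mixed model | Yes |
| EQ-5D | Yes | Covariate, similar approach | Yes |
| Attitude Scale (Tradeoffs) | Yes | Covariate, similar approach | Yes |
| Decision Regret Scale | No | None possible | No |
| SUPPORT (goal concordance) | Yes | No baseline adjustment stated for the GEE | No |
| Clinical Frailty Scale, Pepper tool | Yes | Predictors in exploratory models fitted within each arm | No; only the exploratory models are affected |

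**Step 3: how large could it be?** The article states no figure on this point, so there is none to reproduce. For an analysis that adjusts a follow-up score for its baseline,

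bias ≈ −(slope of follow-up on baseline) × (share of baselines taken after allocation) × (between-arm shift caused by knowing the allocation).

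All three inputs are assumptions: slope 0.3 to 0.7, share 25% to 100%, shift 0.1 to 0.3 SD.

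- Smallest: 0.3 × 0.25 × 0.1 = 0.0075, about 0.01 SD.
- Middle: 0.5 × 0.5 × 0.2 = 0.05 SD.
- Largest: 0.7 × 1.0 × 0.3 = 0.21 SD.
- No shift: zero, whatever the slope and share.

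The bias has the opposite sign to the shift.

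**Step 4: check by simulation.** The setting was a single follow-up score, a true effect of zero, a two-sided 5% test and 4,000 runs per scenario. Group sizes were 131 (the planned number) and 98 (131 × 0.75 = 98.25, after the 25% drop-out in the sample size section).

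| Slope | Share late | Shift (SD) | Mean bias (SD), 98 / 131 per group | Type I error, 98 / 131 per group |
|---|---|---|---|---|
| 0.5 | 0 | 0 | −0.001 / −0.001 | 4.9% / 5.6% |
| 0.5 | 0.5 | 0.2 | −0.053 / −0.047 | 7.1% / 6.8% |
| 0.5 | 1.0 | 0.2 | −0.101 / −0.103 | 13.1% / 16.6% |
| 0.5 | 1.0 | 0.3 | −0.150 / −0.149 | 22.5% / 28.2% |
| 0.7 | 1.0 | 0.3 | −0.210 / −0.211 | 52.6% / 65.2% |

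The simulated bias agrees with the formula. The first row represents all baselines taken before randomization. Its error rates are close to 5%, given a simulation standard error of √(0.05 × 0.95 / 4,000), about 0.3 percentage points.

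**The case against.** The strongest reply is that both rules can be obeyed at once: complete the instruments before randomization and also within the footnote's limit. Table 3 lists them in the column for baseline at randomization, the interval from consent to randomization is not stated, and the flow diagram and Manual of Procedures are not at hand. Late completion is thus permitted, not shown to happen. That stands. It does not remove the conflict, because the surgery limit would be redundant if completion before randomization were enforced.

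Several stronger readings are tempting, and the documents do not support them.

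- **That patients know their arm when they answer.** The article says the assignment goes to the surgical team and that providers and investigators cannot be blinded. It does not say when the participant is told. The inference is plausible but remains an inference.
- **That every patient-reported comparison is affected.** Only three instruments are, as set out in the working.
- **That late frailty scoring biases the treatment comparison.** The Clinical Frailty Scale and Pepper tool are not covariates in the patient-reported models, and the exploratory models that use them are fitted within each arm.
- **That a given bias can be expected.** Slope, share and shift have no source in the article. A shift is also not equally likely for each instrument; a general health measure such as EQ-5D may react less than access satisfaction.

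It is also fair to say that the handling of late baselines may be settled in an analysis plan that is not shown. The two conflicting collection rules, however, stand in this article.

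**Conclusion.** The point holds as an inconsistency with a possible, unmeasured consequence. The main text requires questionnaires before randomization; footnote # to Table 3 allows baseline instruments until index surgery or 10 working days after consent, whichever is earlier, and so permits completion after open allocation.

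If knowledge of the arm shifts answers differently between groups, the adjusted comparisons for the Vascular Access Questionnaire, EQ-5D and Attitude Scale could be biased. Over the assumed ranges the size runs from about 0.01 to 0.21 SD, and neither size nor direction can be fixed from the documents. The upper end needs every baseline to be late, together with a steep slope and a large shift.

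The Clinical Frailty Scale and Pepper tool could likewise be rated with the arm known, with consequences only for the exploratory within-arm models. The primary outcome (CVC-free days), Decision Regret and the goal-concordance analysis are not affected by this mechanism. Confidence is high in the conflict between the two rules and low in any particular amount of bias.

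**What to change.** Reword footnote # to agree with the main text, so that all baseline instruments it marks, including the Clinical Frailty Scale and Pepper tool, are completed before randomization. The most reliable safeguard is to open the REDCap randomization form only once those instruments are entered; randomization already runs through that platform.

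For participants already enrolled, compare each instrument's completion date with the randomization date and flag those that are later. Add a sensitivity analysis for the three affected instruments that does not adjust for the flagged baselines, for example by treating them as missing and modeling baseline and follow-up scores jointly.

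The cost is a change of wording, a form rule in REDCap and one extra analysis. Randomization may occasionally have to wait for the interview. The article reports that the trial is still enrolling, so the change can protect the participants yet to be randomized.
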